## Abstract

Treatment discontinuation, including loss to follow-up (LTFU), is an important challenge for TB treatment, particularly for multidrug- or rifampicin-resistant TB (MDR/RR-TB). Evidence from low-incidence countries evaluating risk factors for unsuccessful outcomes is scarce. Our study aims to examine treatment outcomes and factors associated with treatment discontinuation for MDR/RR-TB patients in the German health care setting. This observational prospective, multi-centre cohort study will enrol 150 MDR/RR-TB patients in treatment centres between 2025 and 2027. Primary outcome is the description of treatment results. Exploratory analyses will be performed, including logistic regression to assess demographic, clinical, and important factors like social determinants possibly associated with treatment discontinuation. Secondary outcomes will include the descriptive analysis of outcomes and safety of the recently recommended 6–9 months and longer MDR/RR-TB regimens, barriers for adherence to TB guidelines and the clinical structures for MDR/RR-TB management. The prospective No1Lost MDR/RR-TB cohort study will improve the understanding of risk factors and barriers for treatment discontinuation and LTFU in a low-incidence setting to address high rates of treatment discontinuation in this vulnerable population with targeted interventions.

Germany is a low-incidence country for TB with a high-resource health care system. Nevertheless, treatment success for TB remains below WHO targets with 63% in 2022.^1,2^ Inconclusive treatment results due to patients transferred to unknown destinations (5.1%) or treatment discontinuation for other reasons (3.2%) are major drivers for unsuccessful TB treatment results.^3^ Early TB treatment discontinuation increases the risk of treatment failure, antibiotic resistance, and transmission of resistant TB strains.^4^ Factors associated with TB treatment discontinuation include older age, alcohol and drug use, poor health literacy, drug adverse events, treatment length, and lack of social support, especially in contexts marked by socio-economic, legal, and structural challenges, such as homelessness and uncertain immigration status.^5–10^ However, published data mainly originate from countries with high TB incidence and cannot always be applied to low-incidence health care settings. To our knowledge, no prospective studies examining the impact of social determinants on TB treatment outcomes have been conducted in high-income, low-incidence settings. Multidrug- or rifampicin-resistant TB (MDR/RR-TB) patients are at increased risk of treatment discontinuation.^4^ A retrospective analysis of two German treatment centres showed 25% inconclusive treatment outcomes due to transfer and loss to follow-up (LTFU) with individualised MDR/RR treatment of 20 months (median).^11^ Shorter and more tolerable regimens like BPaL/M (bedaquiline, pretomanid, and linezolid with or without moxifloxacin) promise fewer side effects and higher rates of treatment completion.^12,13^

Since 2022, the WHO guidelines prioritise the use of the 6-month BPaL/M regimens for treatment of MDR-TB. Despite challenges with the implementation of this pretomanid-containing regimen, the recommendation was adopted for MDR/RR-TB in Germany in 2023.^14^ Other shortened 6- and 9-month treatment regimens based on the results of EndTB^15^ and BEAT-TB^16^ trials were included in the updated WHO guidelines 2025, and further adoption of national guidelines will be necessary.^17^ Recent study data and the evolution of guidelines will lead to a variety of different treatment options for MDR/RR-TB. However, data on the impact of shortened regimens like BPaLM on treatment outcomes and adherence in low-incidence countries are limited^18^ and not yet available for the new 6- and 9-month treatment regimens.

Both, national and international guidelines emphasise the role of comprehensive care and social support in preventing treatment discontinuation.^17,19^ However, health care providers often struggle to meet the complex sociomedical needs of TB patients in everyday care.^20^ Psychosocial support and overcoming language and structural barriers involve substantial effort. Additionally, migration-related factors, such as residence permit issues and legal requirements, may force patients to relocate during treatment. Financial and political reasons may also lead to cross-border relocation, further complicating follow-up.^20,21^ A recent meta-analysis found that migrants have a 4.3 times higher risk of LTFU during TB treatment compared to the non-migrant population in Europe.^22^ Therefore, German guidelines emphasise the need to provide comprehensive care, if possible, in specialised MDR/RR-TB treatment centres providing the necessary treatment structures.^14,19^ Given the increased risk of treatment discontinuation, MDR/RR-TB patients represent a vulnerable group for research and targeted interventions aimed at improving treatment adherence to avoid unsuccessful treatment outcomes.

In July 2024, the study project ‘No1Lost’ was initiated to explore the reasons for TB treatment discontinuation/LTFU with a strong interest in the relevant multifaceted social determinants. No1Lost is a joint project of CAPNETZ STIFTUNG, the Justus Liebig University (JLU), and the German Central Committee against Tuberculosis (DZK), supported by the German Federal Ministry of Health. As part of No1Lost, the MDR/RR-TB cohort study described in this study protocol analyses prospective quantitative data in the vulnerable subgroup of MDR/RR-TB patients. At the same time, qualitative data will be collected by structured interviews with TB patients in Germany both within and outside the MDR/RR-TB cohort to include the patients’ perspectives.

## STUDY OBJECTIVES

The primary aim of this prospective MDR/RR-TB-cohort study is:to describe treatment outcomes and analyse factors associated with treatment discontinuation/LTFU among MDR/RR-TB patients in German TB treatment centres.The secondary aims were to describe:the use, outcomes, and safety of the different available MDR/RR-TB treatment regimens in Germany,adherence to German TB guidelines and explore possible barriers in the German health care system,local treatment structures in German treatment centres relevant for the management of MDR/RR-TB.

## METHODS

### Study design

This is a prospective, observational, multi-centre cohort study. Patients will be observed from January 2025 to December 2027 in German TB treatment centres, recruited from a network of at present 72 clinics available for MDR/RR-TB treatment.^23^ After assessment of feasibility, including number of MDR/RR-TB patients in the last 5 years and prerequisites for successful study implementation, 23 TB treatment centres have been recruited for the study to date. Based on prior case notifications, we expect to enrol approximately 150 patients into the prospective cohort.

### Participants

All patients aged 18 years or older starting MDR/RR-TB treatment at the participating TB centres are considered eligible for the prospective cohort, if written informed consent can be provided. Exclusion criteria include concurrent participation in an interventional study as well as restrictions due to which it is not possible for the patient to give informed consent to participate in the study or to understand and comply with the study requirements. In the event of non-participation, the reasons for study exclusion will be documented and reported.

### Sample size

In Germany, 166 cases of MDR/RR-TB were registered in 2022, an increase from 97 cases attributed to the ongoing war in Ukraine.^3^ This number of cases increased to 208 in 2023.^1^ Data for 2024 are not published yet, but numbers are projected to decline below 200 cases. Based on surveillance data, we anticipate an average of approximately 150 MDR/RR-TB cases per year in 2025–2027. The results of a preparatory workshop and online surveys led us to the assumption that 20 clinics treat over 70% of all MDR/RR-TB cases in Germany. The treatment centres with the highest number of MDR/RR-TB cases participate in the study. Based on our estimates, it will be possible to include 150 MDR/RR-TB cases within the study period, considering the non-participating centres.

### Data collection

For the prospective cohort, routine clinical data concerning TB disease and treatment, along with demographic, sociomedical, radiology, microbiology, and laboratory data, will be collected at hospital admission (baseline, T0) and discharge (T1). During outpatient treatment, follow-up data will be collected every 3 months, restricted to TB treatment, radiology, and microbiology data until a treatment outcome is documented (T2). Post-treatment follow-ups occur every 6 months after treatment completion and include data on outcome changes, recurrence, and post-TB lung disease (T3) (Figure).

**Figure. fig1:**

Data collection procedures in the No1Lost MDR/RR-TB-cohort study. MDR/RR-TB = multidrug- and rifampicin-resistant TB; T0–3 = time points 0 to 3.

The study physicians responsible for data collection will be trained through on-site and virtual preparatory meetings to manage a web-based portal using standardised electronic Case Report Forms (eCRFs). The German guideline recommends monthly consultations between outpatient facilities and TB treatment centres,^14,19^ facilitating data collection for the T2 and T3 follow-ups.

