### Outcomes and measurements

#### Aim 1

To describe MDR/RR-TB treatment outcomes in German TB centres and to analyse known and discussed factors (covariates) associated with treatment discontinuation. The primary outcome measure for Aim 1 is treatment outcome at the end of MDR/RR-TB treatment, according to the updated WHO definitions.^24^ Successful treatment outcomes include ‘treatment completed’ and ‘cured’. ‘Treatment completed’ applies to patients who finish treatment according to guidelines without falling into the category of unsuccessful treatment, while ‘cured’ requires sustainable microbiological conversion of sputum cultures. Unsuccessful treatment outcomes include ‘died’, ‘treatment failed’, ‘lost to follow-up (LTFU)’, and ‘not evaluated’. Follow-ups after treatment completion are not included in this definition and will not be part of the primary analysis. Nevertheless, during post-treatment follow-ups (T3) relapses will be documented. Treatment interruptions of more than 2 months classify as treatment discontinuation, and if no further information on disease progression or whereabouts is available, patients are classified as LTFU. The category ‘not evaluated’ includes patients where no treatment outcome is assigned due to relocation.^24^ For transfers within the study cohort, data collection will continue until a definitive outcome is documented.

Covariates are used for cohort characterisation and as independent or confounding variables in the statistical analysis. They were selected based on known risk factors for unsuccessful treatment and discontinuation in the literature^5–9^ such as demographic data (e.g., age), health-related factors (e.g., smoking, alcohol use, drug use, comorbidities, and co-infections), and clinical as well as microbiological parameters like the extent of TB disease and sputum smear positivity. Additional covariates represent suspected risk factors, like social determinants and structural barriers, discussed in a preparatory workshop with a diverse group of stakeholders in German public health, clinics, ambulatory care, and social work. These include social determinants such as residency status, socio-economic status, living conditions, and insurance coverage (Table).

**Table. tbl1:** Study aims, collected outcomes variables, and corresponding time of data collection in the No1Lost MDR/RR-TB cohort study.

Aims	Outcomes variables	Prospective cohort		
		T0	T1	T2, T3

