To describe the use, outcomes, and safety of different MDR/RR-TB treatment regimens in German TB centres. Outcomes relevant to Aim 2 include the above mentioned MDR/RR-TB treatment outcome according to WHO definitions^24^ depending on different MDR/RR-TB treatment regimens. Safety will be monitored through systematic documentation of adverse events (e.g., allergic reactions, skin discolouration, polyneuropathy, impaired vision, nausea, psychological alterations, hepatotoxicity, prolonged QTc time, anaemia and other forms of myelosuppression, and renal insufficiency), as well as major complications such as TB-IRIS. Clinical laboratory data and imaging results will support the safety evaluation. The Division of Acquired Immunodeficiency Syndrome (DAVIS) table for grading the severity of adult and paediatric adverse event was used for safety evaluation.

#### Aim 3

To describe adherence to German TB guidelines and explore possible barriers in the participating TB centres. A set of performance indicators will be selected by a panel of guideline authors based on relevance, scientific soundness, and feasibility as described by the Association of the Scientific Medical Societies in Germany (AWMF)^31^ for Aim 3. Staff Interviews based on the results of interim analyses will be used to generate qualitative data to explore reasons and possible barriers for non-adherence to German guidelines.

#### Aim 4

To describe the clinical treatment structures for MDR/RR-TB treatment in the participating TB centres. Covariates relevant to Aim 4, such as hospital size, geographical setting (urban/rural), local network structures, hospital sponsorship, the availability of specialised departments for MDR/RR-TB treatment and facilities for TB treatment and support, infection control measures, and the use of assessment tools, for example, for quality of life, will be used to describe MDR/RR-TB-treatment structures in the participating TB centres. A comprehensive overview of outcomes, covariates, and the corresponding time points of data collection (T0–T3) is provided in Table.

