### Statistical analysis

Main outcomes (defined in aims 1–4 above: 1) MDR/RR-TB treatment outcome, 2) outcomes and safety of different MDR/RR-TB regimens, 3) guideline adherence, and 4) relevant structures for MDR/RR-TB treatment) as well as covariates (demographic, health-related, sociomedical, and clinical parameters) will be analysed using descriptive statistics. Nominal data will be presented with absolute and relative frequencies, continuous data with means and standard deviations (±SD), and ordinal or skewed data with medians, first and third quartiles (Q1 and Q3). The sample size was calculated to ensure adequate precision for estimating the primary outcome of treatment discontinuation. Based on previous data,^11^ we anticipate a discontinuation rate of approximately 25%. To estimate this proportion with a 95% confidence interval (CI) margin of error of 7.5% or less, a sample of at least 129 patients is required. Our expected enrolment of approximately 150 MDR/RR-TB patients is therefore feasible and exceeds this minimum requirement. With this sample size, we will be able to estimate an observed rate of 25% with a 95% CI of 18.1%–31.9% (margin of error 6.9%). This level of precision is considered sufficient for the study’s primary objectives of informing future programme planning and intervention design (powermediation package in R). In an exploratory analysis, MDR/RR-TB treatment outcome will be modelled as a binary dependent variable in generalised linear models (e.g., logistic regression) to quantify the effect of relevant demographic, sociomedical, and clinical factors on treatment discontinuation (yes/no). The WHO categories ‘LTFU’ and ‘not evaluated’ will be combined and classified as treatment discontinuation. Effect sizes, such as odds ratios with 95% CIs, will be calculated and reported. To account for clustering effects at the TB centre level, we will also employ generalised estimating equations. All statistical tests will be two-sided, and robust standard errors will be applied to improve variance estimation. A significance threshold of *P* < 0.05 will be used, with adjustments for multiple testing when necessary.

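### Pooling 'not evaluated' with LTFU lets a patient who moves away and continues treatment count as having discontinued it

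*Protocol article*

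**What the plan says.** Data collection: outpatient (T2) data are gathered every 3 months until an outcome is recorded. The text after the figure adds "The German guideline recommends monthly consultations between outpatient facilities and TB treatment centres" and says that this makes T2 and T3 collection easier.

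Outcomes and measurements, Aim 1: an interruption of more than 2 months is a discontinuation, and "if no further information on disease progression or whereabouts is available, patients are classified as LTFU". 'Not evaluated' is for patients given no outcome because they relocated; no interruption is required. On moves between clinics: "For transfers within the study cohort, data collection will continue until a definitive outcome is documented". Nothing comparable is said about moves out of the cohort.

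Statistical analysis: for the logistic model, 'LTFU' and 'not evaluated' are pooled into one yes/no variable, treatment discontinuation. The sample size rests on a 25% discontinuation rate. According to the introduction, the earlier two-centre analysis behind that figure counted transfers and LTFU together as inconclusive outcomes. Generalised estimating equations and robust standard errors are planned for clustering by centre.

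Study design and Sample size: 23 centres have been recruited from a network of 72 clinics, and 20 clinics are assumed to treat over 70% of cases. The introduction expects some patients to relocate during treatment, including across borders.

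**The concern.** The variable called treatment discontinuation contains two different events. One is a patient who stopped treatment. The other is a patient whose outcome did not reach the study, who may have stopped or may be completing treatment elsewhere. Under Aim 1, discontinuation is defined by an interruption. In the analysis it is defined by category, and one of the two categories needs no interruption at all.

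Two results are exposed. The first is the discontinuation rate, whose precision justifies the sample size. The second is the set of associations in the exploratory regression. Residency status, living conditions and similar planned covariates are plausibly linked to moving away. If movers' outcomes are harder to obtain, these covariates will appear to predict stopping treatment even where they predict only a missing report.

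**Working it through.** **The plan's own figures.** Inputs from the statistical analysis section: p = 0.25, margin 0.075, 95% CI.

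- n = 1.96² × 0.25 × 0.75 / 0.075² = 128.05, rounded up to 129. This agrees with "95% confidence interval (CI) margin of error of 7.5% or less, a sample of at least 129 patients is required".
- At n = 150: 1.96 × √(0.25 × 0.75 / 150) = 0.0693, so 18.1% to 31.9%. This also agrees.

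The stated figures are correct. The question is what the 25% counts.

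**Model for missed capture.** Let t be the true discontinuation rate and u the share of patients who did not discontinue but whose outcome is not obtained. Neither split is given in the article, so both are assumptions. The recorded rate is r = t + (1 − t) × u.

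**Effect on the rate, t = 25%:**

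- u = 5%: r = 0.25 + 0.75 × 0.05 = 28.75%, a shift of 3.75 points.
- u = 10%: r = 0.25 + 0.75 × 0.10 = 32.5%, a shift of 7.5 points, against a stated margin of 6.9.

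Since the planning figure is itself a composite of transfers and LTFU, the calculation can be reversed. If 25% is the recorded rate, t = (0.25 − u) / (1 − u). This is 0.20 / 0.95 = 21.1% for u = 5% and 0.15 / 0.90 = 16.7% for u = 10%.

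**Effect on an association.** Take two groups with the same t, and missed capture in one of them only. The spurious odds ratio is [r / (1 − r)] / [t / (1 − t)].

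- t = 25%, u = 5%: (0.2875 / 0.7125) / (0.25 / 0.75) = 1.21.
- t = 25%, u = 10%: (0.325 / 0.675) / (0.25 / 0.75) = 1.44.
- t = 20%: 1.26 and 1.56. t = 15%: 1.35 and 1.74.
- Equal missed capture in both groups (10% and 10%): 1.00. Only the rate is inflated.

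With 75 patients per group and clustering ignored, the two artefacts at t = 25% would reach two-sided P < 0.05 about 7% and 17% of the time. The main harm is thus a shifted estimate rather than frequent false significance.

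**Could the uncaptured part be large?** The only split in the article is for all TB in Germany: 5.1% transferred to unknown destinations and 3.2% other discontinuation. The first is 5.1 / (5.1 + 3.2) = 61% of the two. This is not specific to MDR/RR-TB and serves only to show that the share need not be small.

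**The case against.** A good deal can be said for the plan. The 3-monthly collection does not depend on a consultation having taken place. Data entry is checked for completeness, queries are raised, and missing values are analysed after years 1 and 2. LTFU first requires an interruption of more than 2 months, so missing information alone does not create it. The outcome table lists LTFU and 'not evaluated' separately. The highest-volume centres take part, so at most about 30% of cases are treated outside the 20 largest clinics. Tracing steps may be set out in the full protocol.

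All of this stands, but it does not remove the pooling. Completeness checks find empty fields, and a patient coded 'not evaluated' has a filled one. Separate descriptive counts do not help a regression that uses the pooled variable. Generalised estimating equations and robust standard errors deal with correlation and variance, not with a misclassified outcome.

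A stronger reading is tempting: that capture rests on the guideline contacts, while guideline adherence is itself under study (Aim 3: "To describe adherence to German TB guidelines and explore possible barriers in the participating TB centres"), so that weakly networked sites will record more loss and site structure will emerge as a false risk factor. The article does not support this. The contacts are said only to ease collection. No data show that capture differs between sites. Local network structures are collected for description under Aim 4, and the regression names demographic, sociomedical and clinical factors. 'Structural barriers' do appear among the suspected risk factors, but the examples given are patient-level. Nor does a 3-monthly form necessarily miss a gap of 2 to 3 months, because it can record interruption dates retrospectively.

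**Conclusion.** The point holds in a limited form. As defined, treatment discontinuation can include patients who relocated outside the study centres and continued treatment. This can inflate the estimated rate and bias associations with relocation-related covariates. It would reach site factors only if capture differs by site and such factors are modelled.

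The size is illustrative. Missed capture of 10% would move the rate by 7.5 points at a true rate of 25%. Missed capture of 5% to 10% in one group only would give an odds ratio of 1.21 to 1.44 with no true effect. Both rest on assumed values of t and u. With equal capture across groups no association is created where none exists. The sample size arithmetic is right. It simply does not cover this source of error, which a larger sample would not reduce.

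**What to change.** 1. Within the pooled variable, distinguish 'interruption of more than 2 months confirmed' from 'no outcome information, including relocation or transfer out'. The WHO categories can stay as they are for the descriptive table.
2. Report the discontinuation rate with the second group counted as discontinued, and again with it counted as not discontinued or excluded. Repeat the regression in the same way. An association that survives both codings can be read as concerning treatment; one that appears only under the first may reflect missing reports.
3. Where consent allows, make one logged outcome enquiry to the last outpatient facility or the receiving clinic, in or outside the study, before coding LTFU or 'not evaluated'.

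The cost is a little extra analysis and, at the planned rate, 0.25 × 150 = 37.5, or about 38 enquiries. The consent text may need a line on contacting onward providers. It is best done early, because outcomes not sought at the time may be hard to recover later.
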